#### 4.1.7 Contouring of normal Structures for Cyberknife and MR LINAC

##### Contouring of Normal Tissue Structures

###### Heart

The heart should be contoured beginning just below the level in which the pulmonary trunk branches into the left and right pulmonary arteries (PA). Above the PA, none of the heart's 4 chambers are present. All the mediastinal tissue below this level should be contoured, including the great vessels (ascending and descending aorta, inferior vena cava). The heart should be contoured on every contiguous slice thereafter to its inferior most extent near the diaphragm. If one can identify the esophagus, this structure should be excluded. One need not include pericardial fat, if present. Contouring along the pericardium itself, when visible, is appropriate.

###### Lungs

Both the right and left lungs should be contoured as separate structures. Contouring should be carried out using pulmonary windows.

###### Skin

The skin will be defined as the outer 0.5 cm of the body surface. As such it is a rind of uniform thickness (0.5 cm) which envelopes the entire body in the axial planes. The cranial and caudal surface of the superior and inferior limits of the

planning CT should not be contoured as skin unless skin is actually present in these locations (e.g., the scalp on the top of the head).

#### Ipsilateral and contralateral breast

Each breast is contoured separately. The entire breast mound should be contoured including glandular tissue, intervening fibrous and adipose tissues, subcutaneous fat, and overlying skin and nipple to begin medially adjacent to the sternum, laterally at the mid axillary line or reflection of breast (whichever is more extreme), superiorly below the clavicle or reflection of breast (whichever is more extreme), inferiorly at the inframammary fold or reflection of breast (whichever is more extreme), and centrally at the chest wall/breast interface (not including pectoralis or other deep muscles).

#### Brachial Plexus

The defined ipsilateral brachial plexus originates from the spinal nerves exiting the neuroforamina on the involved side from around C5 to T2. However, for the purposes of this protocol, only the major trunks of the brachial plexus will be contoured using the subclavian and axillary vessels as a surrogate for identifying the location of the brachial plexus. This neurovascular complex will be contoured starting proximally at the bifurcation of the brachiocephalic trunk into the jugular/subclavian veins (or carotid/subclavian arteries) and following along the route of the subclavian vein to the axillary vein ending after the neurovascular structures cross the second rib.

#### Ribs

Only ribs within 4 cm of the treatment volume need to be contoured.

### **4.1.8 Contouring of normal Structures for Gammapod**

Organs at Risk: Organ at risk doses are unable to be calculated in real-time in the treatment planning system for Gammapod. As such, certain isodose lines will be displayed. The physician and physicist will review these isodose lines and their proximity to specific organs including but not limited to the lung, heart, chest wall and skin. Following completion of treatment, dose-volume histogram analysis will occur. The same structures as above in the section 4.1.7 can be done after treatment. If a dose constraint (listed below) is not met, this will be recorded as a deviation. The lung constraints may not be able to be obtained, as for Gammapod treatment it is hard to get the entire lung in view. All plans will undergo central review.

However, during treatment in real time the following can serve as a guide for evaluation of a Gammapod plan in real time.

Heart: the heart will be contoured following treatment as in section 4.1.7. During the treatment planning process, the isodose line representing the 31% isodose line should be displayed. This isodose line should not touch the surface of the heart/pericardium. While in many circumstances in a dose escalation study, the OAR doses would increase with each dose cohort, we will also calculate and record the mean heart dose as this parameter has been found to have significance to the risk of heart disease for women with breast cancer.

Ipsilateral lung: the ipsilateral lung will be contoured following treatment and will include the entire lung within the CT scan. Due to the focused nature of the treatment and the requirement to perform CT simulation with 1 mm slices, the entire lung from apex through the diaphragm. During the treatment planning process, the isodose line representing the 31% prescription isodose line should be displayed. This isodose line should not touch the surface of the lung. As we

will not specifically be scanning through the entire lung, a normal lung DVH cannot be calculated.

Ipsilateral chest wall: the ipsilateral chest wall will include the pectoralis muscles, intercostal muscles and the ribs. As with the other OARs, this will not be contoured during the treatment planning process but will be evaluated afterwards. During the treatment planning process, the 30% isodose line will be displayed. This should not touch the surface of the muscle/rib. In the post-treatment evaluation, the dose constraint of 30 Gy < 30 cm^3 should be evaluated and recorded. This metric has been shown to be an important metric for lung SBRT and correlates with a risk of chest wall pain. Chest wall pain is not common during breast cancer radiation and treatment. As such we want to adopt a similar treatment parameter.

Skin: the skin will be defined as the first 5 mm of skin from the surface into the breast. The TPS will auto contour this from the surface of the inner cup. However, the physician and physicist will need to review this and edit it as the system does not have the ability to auto-contour the silicone bolus, thus this will have to be edited as appropriate. The max dose to the skin surface (true surface) is calculated in real time from the TPS.

#### **4.1.9 Radiation Therapy Quality Assurance Reviews**

The principal Investigator or her designee along with a medical physicist, will perform an RT Quality Assurance Review after complete data for the first 20 cases enrolled has been received at the University of Texas Southwestern. They will perform the next review after complete data for the next 20 cases enrolled has been received at the University of Texas Southwestern. The final cases will be reviewed within 3 months after this study has reached the target accrual or as soon as complete data for all cases enrolled has been received, whichever occurs first.

#### **4.1.10 Potential Risks**

**Potential Risks/Discomfort:** The first risk of participation in the study is that patients may be inappropriately selected for this treatment modality since surgery is not performed first. The primary breast tumor could be larger (or smaller) than what the pre-treatment imaging shows. The patient could have lymph node involvement not detected in their work up but only detected at the time of surgery. To decrease this risk, patients will undergo rigorous screening and work up. Only patients with small, ER+ tumors will be enrolled in the trial. These have a lower risk of lymph node involvement. In the event that the patient's stage or tumor size is higher or larger than what is expected at the time of pathology, further treatment parameters have been recommended within the protocol to ensure that patients receive appropriate treatment.

The second risk in this study is a risk of increased surgical morbidity. Pre-operative partial breast trials to date show rates of surgical morbidity that are equivalent or in line with the standard of care. There have been minimal wound healing complications. Seromas have been noted, however, the incidence of these in the currently available literature is no different than standard series.

Finally, there is a potential risk of a worse cosmetic outcome in the short or long term. While there are no convincing data to suggest such an outcome based on the currently available literature, there has not been 10 year follow up with this treatment paradigm.

## 4.2 Toxicities and Dosing Delays/Dose Modifications

Any subject who receives treatment on this protocol will be evaluable for toxicity. Each patient will be assessed for the development of toxicity according to the Time and Events table in Section 5.4. Toxicity will be assessed according to the NCI Common Toxicity Criteria for Adverse Events (CTCAE), version 5.0. Dose adjustments should be made according to the system showing the greatest degree of toxicity.

## 4.3 Concomitant Medications/Treatments

### 4.3.1 Systemic and Adjuvant Surgery

#### Systemic Therapy

Use of endocrine therapy after pre-operative radiation should be started within 21 days after pre-operative radiation, but it is encouraged to start the day after the post-radiation biopsy. Typically, for estrogen/progesterone positive patients, many will start endocrine therapy as they are waiting for surgery. Oncotype or Mammprint studies should be done on the biopsy specimen, if possible, prior to delivery of radiation if there is adequate tissue. If not, patient may require another biopsy to obtain this tissue and this will be at the discretion of the medical oncologist.

Surgery: Surgery can be done anytime from 8 to 52 weeks at the discretion of the surgeon. Sentinel lymph node biopsy can be done at time of lumpectomy or if patient prefers mastectomy.

Sentinel lymph node mapping: in the previous University of Maryland pre-operative study there were no instances of failed sentinel lymph node mapping on the 25 patients treated on the trial. Based on this experience, we have no reason to think that there should be an increase in failed mappings with the pre-operative radiation treatment. A peri-tumoral, intra-dermal or peri-areolar injection are allowed based on the discretion of the breast surgeon.

Sentinel lymph node mapping exclusions: In the elderly population (defined differently in by different trials and also based on medical comorbidities), a sentinel lymph node procedure is often not performed on low-risk patients. In this trial, we will not require women 70+ to have a sentinel lymph node mapping if it is deemed unnecessary by their treatment team. This must be documented in the patient's medical record.

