## STUDY SCHEMA

### Phase I Study of Pre-Operative Stereotactic Partial Breast Irradiation Therapy for Early Stage Breast Cancer

[figure not shown]

\*\*Of note, after pre-operative radiation and prior to surgery, patients should start endocrine therapy within 21 days after pre-operative radiation but it is encouraged to start the day after post-radiation biopsy.

Prescription will be 30 Gy to the Planning Target Volume (PTV) for all dose cohorts, and either 30 Gy, 34 Gy, or 38 Gy to the GTV/CTV per appropriate dose cohort.

Number of patients= between 7-60 for phase I (depending on tolerance)

All patients in each dose cohort will be treated as a single group for dose escalation. The starting dose for the dose escalation portion will be 30 Gy. Subsequent cohorts of patients will receive an additional 4 Gy per treatment. If significant toxicity is encountered at the starting dose, a de-escalation will occur (step -1) to 26.5 Gy. As we are currently concluding an adjuvant single fraction phase I protocol (ClinicalTrials.gov Identifier: NCT02685332) to 30 Gy in a single fraction for early stage breast cancer, if we meet our endpoints of this study, we will start our dose escalation at 34 Gy instead of the 30 Gy, as safety of the 30 Gy arm will have already been established.

| Level | Dose    | No. of Patients |
|-------|---------|-----------------|
| -1    | 26.5 Gy | 7-15            |
| 1     | 30 Gy   | 7-15            |
| 2     | 34 Gy   | 7-15            |
| 3     | 38 Gy   | 7-15            |

- Prescription will be a minimum of 27 Gy to the PTV for all dose cohorts, and either 30 Gy, 34 Gy, or 38 Gy to the GTV/CTV per appropriate dose cohort. See section 4.1.5

Minimum waiting periods will be assigned between each dose cohort to evaluate toxicity. The phase I study will be completed when dose limiting toxicity is reached or when delivery of a pre-determined highest dose of radiation (38 Gy) that has been deemed likely to be efficacious for treatment of early stage breast cancer is attained.

At the time of writing this protocol, the current single fraction trial being tested in the adjuvant setting for early stage breast cancer is 30 Gy in 1 fraction at UTSW (NCT02685332). If we meet our accrual goal and waiting period without a dose limiting toxicity by the time this protocol is ready to go live, we will start our dose for this trial at 34 Gy.

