### 1.3 Study Rationale

Given interest in preoperative S-PBI, there have been several recently initiated preoperative S-PBI trials that have opened and are ongoing (see Table 1). However, these ongoing preoperative trials are predominantly using doses seen in the adjuvant setting as established with IORT, primarily 21Gy/1Fx, although a 3-fraction and 5-fraction regimen are also currently being investigated at Moffit (NCT03137693) and the Juravinski Cancer Center (NCT02065960), respectively. Pathologic complete response rates with three-fraction preoperative S-PBI have been reported to be 36%, with the highest pCR rate of 67% in the 25.5Gy/3Fx cohort, though this cohort was small with only 6 patients (Bondiau IJROBP 2013), suggesting room for improvement. At ESTRO in 4-2019, the results from the Netherlands (clinical trials.gov: NCT0231661) ABLATIVE trial treating patients with Estrogen positive her2- tumors and 20 Gy preoperative radiation yielded a path CR of 33% at 6 months and 41% at 8 months with mild treatment toxicity (ESTRO abstract OC-0591 Vasmel et al.)

As predicted by the universal survival curve, 38Gy/1Fx would be equivalent to 70Gy/35Fx, a dose that is typically used for gross disease (Park IJROBP 2008). Given that these early studies have reported minimal toxicity with the addition of preoperative S-PBI, this offers promise that further dose escalation to achieve a radioablative dose adequate for gross disease may be feasible.

Therefore, the purpose of this phase I trial is to evaluate dose-limiting toxicity while dose escalating single-fraction preoperative S-PBI to a presumed radioablative dose over 3 cohorts, starting with 30Gy in 1 fraction and advancing to 34Gy and 38Gy in 1 fraction. This would be accomplished on the MR Linac, CyberKnife, or GammaPod. The GammaPod is a novel device dedicated to S-PBI utilizing a Cobalt-60 source (Yu Med Phys 2013), which offers a highly reproducible prone setup with a mean of 1.8mm of mismatch reported in 15 patients at the University of Maryland on consecutive scans (Yu JCO 2011). Implications of this research are far reaching, including determination of the maximally tolerated dose for preoperative S-PBI, pathologic complete response rates of early stage breast cancer to a predicted radioablative dose, radiographic markers of treatment response (radiomics), and translational research assessing mechanisms of immune and radiation response.

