### 2.3 Exploratory Objectives

#### 2.3.1 Radiomics on MRI

Through extracting and analyzing a large number of features from medical imaging, radiomics has shown promising results in treatment outcome prediction for many diseases including breast cancer (45-50). UTSW physics group has developed several new radiomic approaches and radiomic features, such as a multi-objective radiomics model (51) and a new radiomic "Shell" feature (52). As an exploratory end point for this trial, we will explore the application radiomics using pre-treatment MRI, treatment parameters and clinical characteristics as input to predict pathological response of radiation therapy (XRT) based on pathology report of surgical tissues and local recurrence.

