#### **MRI Time Points**

Two MRIs will be performed for each participant at the following points:

- MRI1: (baseline) prior to the start of neoadjuvant treatment. Any additional lesions identified on MRI will be addressed per standard of patient care. If patient cannot have MRI, contrast enhanced digital mammography(CEDM) is allowed in place of MRI.

- MRI2 (optional but highly recommended): (*post Gammapod, MR Linac, or Cyberknife*) After MRI1, before surgical excision. The purpose of this optional scan is to test response to radiotherapy.

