### **5.2.2 Within 14 days (+2 days) after Radiation**

- Optional tumor sample

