4 Baseline MRI or contrast enhanced digital mammography(CEDM) is required, Post-radiation MRI is optional but highly recommended and if done, post radiation MRI must be completed at least four weeks after XRT and before surgery.

5 Completed via phone evaluation by study team member

6 Optional tumor sample collection can be done within +2 days of time point above

7 Archival or diagnostic tumor samples

8 Optional tumor sample to be completed within 30 days prior to radiation

9 Should be taken prior to radiation therapy

10 Patient and Physician cosmesis can be completed any time after consent but prior to radiation treatment

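### Readouts labelled as response to radiation are, on the protocol's own schedule, responses to radiation plus endocrine therapy: about 1 to 52 weeks of it at the follow-up MRI and about 5 to 52 weeks at surgery

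*Protocol*

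**What the plan says.** **Timing.** Eligibility (3.1) requires hormone-receptor-positive, HER2-negative disease with no earlier endocrine treatment for it. On endocrine therapy, 4.3.1 says: "Use of endocrine therapy after pre-operative radiation should be started within 21 days after pre-operative radiation". The Study Schema fixes the order: "after pre-operative radiation and prior to surgery, patients should start endocrine therapy within 21 days after pre-operative radiation". Section 4.3.1 adds a preference: "it is encouraged to start the day after the post-radiation biopsy". That biopsy is optional, and 5.2.2 times it as "Within 14 days (+2 days) after Radiation". For the second MRI (MRI2, also optional), 5.4 footnote 4 states: "post radiation MRI must be completed at least four weeks after XRT and before surgery". Surgery falls at 8 to 52 weeks, at the surgeon's discretion (4.3.1), counted from radiation (8.1).

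**Labels.** On MRI2, 5.1.14 says: "The purpose of this optional scan is to test response to radiotherapy". Section 6.1.2 likewise presents the MRI assessment as one of response to the stereotactic radiotherapy. The radiomics objective (2.3.1) is "to predict pathological response of radiation therapy (XRT) based on pathology report of surgical tissues and local recurrence". Among the expected yields of the trial, 1.3 lists "pathologic complete response rates of early stage breast cancer to a predicted radioablative dose".

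**Analysis.** Section 10.3 plans one overall complete response rate with an exact 95% interval. Section 6.1.2 plans logistic regression of response on imaging parameters. Neither mentions endocrine therapy or the interval from radiation to surgery.

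**The concern.** In this population endocrine therapy is an antitumour treatment given between radiation and the readout. If it has been running before the follow-up MRI and before the specimen is examined, any change seen there belongs to the combination. Attributing it to the radiation dose claims more than the design can show.

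The length of exposure is not fixed either. It is set mainly by the surgery date, so patients pooled in one response rate may have had very different amounts of the second treatment.

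At stake is what may be concluded from a secondary endpoint (pCR) and from the imaging and tissue work, not the dose-escalation decision. A pCR rate from this trial could be published as the ablative effect of 30, 34 or 38 Gy when the data support a statement only about that dose followed by endocrine therapy.

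**Working it through.** The plan states no figure to reproduce, so the check is timeline arithmetic. Day 0 is radiation.

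**Inputs**
- Latest recommended endocrine start: day 21 (Study Schema, 4.3.1, 8.1).
- Earliest start: the protocol sets none. Day 1 is assumed.
- Encouraged start: the day after the biopsy. For a biopsy on days 14 to 16 this is day 15 to 17.
- Earliest MRI2: day 28 (5.4). Latest: just before surgery.
- Surgery: day 56 to day 364 (4.3.1, 8.1).

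**Formulas.** Minimum exposure = earliest readout day − latest start day. Maximum exposure = latest readout day − earliest start day.

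| Readout | Minimum | Maximum | With encouraged start (day 15–17) |
|---|---|---|---|
| MRI2 | 28 − 21 = 7 days (1.0 week) | 364 − 1 = 363 days (51.9 weeks) | (28 − 17)/7 = 1.6 to (364 − 15)/7 = 49.9 weeks |
| pCR and surgical tissue | 56 − 21 = 35 days (5.0 weeks) | 363 days (51.9 weeks) | (56 − 17)/7 = 5.6 to 49.9 weeks |

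The 1-week minimum applies to MRI2 only.

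**Share of the interval and spread, for a day-21 start**
- Surgery at week 8: 35/56 = 62.5% of the radiation-to-surgery interval is on endocrine therapy.
- Surgery at week 52: (364 − 21)/364 = 343/364 = 94.2%.
- Ratio of exposures: 343/35 = 9.8, about tenfold between patients who both follow the schedule.

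**Can adjustment separate the two?** Days on endocrine therapy = surgery day − start day. The start can vary over 21 − 1 = 20 days and surgery over 364 − 56 = 308 days (44 weeks). If the two are taken as independent and uniform, each variance is range²/12, and the correlation of endocrine days with the radiation-to-surgery interval is √[308²/(308² + 20²)] = √(94,864/95,264) = 0.998. If surgery dates in practice spanned only 8 weeks (56 days), it would be √[56²/(56² + 20²)] = √(3,136/3,536) = 0.94. The uniform spread and the 8-week span are assumptions. Either way the two quantities are nearly the same variable.

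The interval may matter by itself. Section 1.3 cites a study of 20 Gy preoperative radiation with pCR of 33% at 6 months and 41% at 8 months. The protocol does not say what those patients received between radiation and surgery.

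**Data capture.** Medications are reviewed at screening (5.1.5). The later visit lists (5.2) and the Time and Events Table (5.4) have no item for endocrine agent or start date.

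**The case against.** Much of the case on the other side stands, and it limits the point.

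- **The formal objective is neutral.** Section 2.2.5 and the endpoint list in 10.1 name only pCR rates, and 10.3 reports one overall rate. The attribution to dose is in the rationale (1.3). This stands: 2.2.5 and 10.3 state nothing wrong. The labels in 2.3.1, 5.1.14 and 6.1.2 remain.
- **No dose comparison of pCR is planned.** A reader might infer that a pCR trend across 30, 34 and 38 Gy will be confounded by longer waits in later cohorts. The documents plan no such test and give no sign that waits will lengthen, so this is a caution for interpretation only.
- **Not every patient need be exposed.** A reader might infer that all readings are taken on endocrine therapy. The start is a recommendation, and 4.3.1 says only that many patients begin while awaiting surgery. Some may have none, which widens the variation.
- **The biopsy is largely protected.** The encouraged start after the post-radiation biopsy keeps that sample free of endocrine therapy when followed. It is not guaranteed, because only a latest start is set.
- **Radiomics inputs are broad.** Section 2.3.1 admits treatment parameters and clinical characteristics, so endocrine exposure could enter the model, and baseline MRI features are unaffected. The name of the outcome would still be wrong.
- **The MRI–pathology association is not invalidated.** MRI2 and surgical pathology are both read after the same treatments. Only the first sentence of the MRI Analysis paragraph is limited to univariate models, and covariates may be left to an analysis plan that is not shown.
- **Case report forms are not shown.** The absence of an item from the visit lists does not prove that the date will go unrecorded.

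**Conclusion.** The point holds as one of labelling and interpretation. For a patient who follows the schedule, endocrine therapy has run for about 1 to 52 weeks at MRI2 and about 5 to 52 weeks at surgery, while 2.3.1, 5.1.14 and 6.1.2 name the result as response to radiation and 1.3 links pCR to the radiation dose. With no endocrine-free group, no analysis of these data can recover the effect of radiation alone.

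The ranges assume that the recommended day-21 limit and the 8-to-52-week surgery window are kept, with day 1 as the earliest start. They measure exposure, not bias: the documents do not say how much endocrine therapy contributes to pCR, so the size of any misattribution cannot be given. A reader might also infer that adding endocrine days as a covariate would isolate radiation. It would not, because those days almost coincide with the time since radiation.

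The affected readouts are secondary or exploratory, and MRI2 is optional. The primary endpoint, dose-limiting toxicity and the maximum tolerated dose, is untouched. The change is worth making because it alters what the trial may conclude at almost no cost.

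**What to change.** Leave care as it is, and change the description and the reporting.

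1. In 2.3.1, 5.1.14 and 6.1.2, and wherever the complete response rate from 10.3 is interpreted, restate the quantity as response to single-fraction radiation followed by endocrine therapy.
2. Record the endocrine agent and start date for each patient, including those who do not start before surgery.
3. Report pCR and MRI response descriptively alongside days on endocrine therapy and the radiation-to-surgery interval. State that the two are nearly collinear and that adjustment can neither separate them nor isolate radiation.
4. Describe the optional post-radiation biopsy as radiation-only only when it was taken before endocrine therapy began.

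The cost is wording, two data fields and a descriptive table. The downside is a narrower claim about radiation alone, which is the claim the design can support.
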